## Abstract

**Background:**

Parkinson disease (PD) has been described and studied extensively in White populations, with little known about how the disease manifests and progresses in patients from the Black community. Studies investigating disease features in Black populations are uncommon, with some suggesting that the Black population with PD is more disabled and has greater disease severity and different clinical features compared with the White population with PD. These health disparities are likely to influence the quality of care for Black patients with PD.

**Objective:**

This study aimed to investigate the motor and nonmotor symptoms and quality of life in Black and White participants with PD in a case-case design.

**Methods:**

This is an observational, prospective, multicenter, case-case design study. Other aims will investigate the management of PD in Black individuals and the presence of shared or unique genetic risk factors among the Black PD population. A total of 400 Black and 200 White participants with PD will be recruited. Data will be collected at 7 US sites and entered into a Research Electronic Data Capture database. Linear multivariate regression analysis will be used, except for comparing PD management, which will be analyzed using the chi-square test or Fisher exact test. Bonferroni correction will be applied. This protocol also describes plans for educational programming for clinicians and patients at the end of the study in partnership with national PD organizations.

**Results:**

The Rush Institutional Review Board approved the project as the single-site institutional review board in February 2022, and it was funded by the National Institute of Neurological Disorders and Stroke in April 2022. Recruitment began in July 2022. At the time of submission of this manuscript, 131 participants had been recruited.

**Conclusions:**

To our knowledge, this is the largest study of PD phenotype and management in Black patients in the United States. The planned collaboration with the Global Parkinson’s Genetics Program and PD GENEration will enhance our understanding of genetic risk factors for PD in this understudied population.

**International Registered Report Identifier (IRRID):**

DERR1-10.2196/60587

## Introduction

### Background

Parkinson disease (PD) is a progressive and incurable neurodegenerative disorder affecting 1 million people in the United States [1]. Health care resource usage costs for patients with PD in the United States are high and rise 2 to 3-fold in individuals with advanced disease [2]. Our current understanding of PD is disproportionately based on studying populations of European ancestry, leading to a significant gap in our knowledge about the clinical characteristics, life experiences, functional outcomes, and pathophysiology in individuals of African descent. The cumulative incidence of PD in African Americans has been estimated at 23/100,000, compared with 54/100,000 in European Americans [3]. Direct comparison of Black and White patients suggests greater disability and disease severity in Black individuals [4], and our data suggest that quantitative measures may be more sensitive in detecting these differences [5]. Factors proposed to account for phenotypic differences include barriers to access to care and methodological confounds due to inconsistent diagnostic criteria or ascertainment bias [6-8]. It is also possible that population-specific genetic variation modifies PD risk and clinical manifestations of PD in Black individuals. Approximately 90 common susceptibility loci for PD and a growing number of rare gene variants are now well-established in White populations [9]. Still, the impact of these factors on the Black population is largely unknown.

In our pilot work, Black and White patients with PD participated in a clinical phenotyping study, and the results showed no significant differences between the groups in sex, education, disease duration, Hoehn and Yahr stage, or Movement Disorder Society-Unified PD Rating Scale (MDS-UPDRS) part III Motor scores [10]. However, quantitative NIH Toolbox performance measures detected differences in gait and balance between Black and White participants with PD: gait speed (0.8±0.3 vs 1.1±0.2, *P*<.001), pegboard (41.4±15.6 vs 33.2±10.9, *P*=.04, and standing balance (32.7±13.1 vs 47±12, *P*<.01) [5]. In the nonmotor assessments, the Montreal Cognitive Assessment (23.4±3.1 vs 27±2.1, *P*<.005) and Symbol Digits Modalities Test (39.4±14.1 vs 49.6±9.1, *P*=.01) scores were worse in Black participants after correcting for education level. Hamilton Depression scale scores were worse in Black participants with PD compared with White participants (7±5.6 vs 4±3.5, *P*=.04), but other neuropsychiatric scales were similar between groups. The PD Quality of Life (PDQ-39) scores were higher (worse) in Black participants with worse ratings in participation in social roles and activities.

In summary, this pilot data showed differences in the motor examination, nonmotor features, and quality of life of Black patients with PD that warranted the current larger study. In our previous work and this protocol, race is self-identified by the patient as Black or White. Traditionally in the Chicago metropolitan area, this includes Black patients who are African, Afro-Caribbean, African American, or who report a mixture of races.

Racial disparities in the clinical management of PD include inequitable access to care and disparities in therapeutic interventions. Previous studies show that Black individuals with parkinsonism are less likely to see a neurologist, have less access to telemedicine, and are less likely to receive treatment, including antiparkinsonian medication, surgical procedures, and rehabilitation therapy. Black patients are 30% less likely to see an outpatient neurologist for neurologic conditions [11], and both Black persons and those with lower socioeconomic status are less likely to receive specialized care for PD [4]. Compared with White persons with PD, Black patients with PD were 40% less likely to receive any rehabilitation therapy (physical therapy, occupational therapy, and speech therapy). Black persons with parkinsonism were less likely to be receiving any antiparkinsonian medication on their initial visit to a movement disorders center [12]. They were half as likely to receive newer antiparkinsonian medications but twice as likely to be on antipsychotic medication. African Americans were 4 times less likely to receive any treatment for PD (medication or physical therapy) in a cohort with the same health care insurance (Medicaid) [13], and White persons were nearly twice as likely to be prescribed medications for PD in a study of racial disparities in stroke (National Institute of Neurological Disorders and Stroke [NINDS] Reasons for Geographic and Racial Differences in Stroke study) [14]. African Americans were also found to be 5 to 8 times less likely to undergo deep brain stimulation surgery for PD than White patients [15,16]. Notably, racial disparities in access to care and clinical management are likely to be associated with adverse outcomes, including greater severity of Parkinsonian symptoms and greater disability [4].

Genetic susceptibility loci and genetic variants causing monogenic PD have been explored in populations of European, Latino, and Asian ancestry [17]. Based on preliminary work, it appears that the cumulative genetic risk for Black and African American patients with PD shows significantly different distributions compared with European populations when applying the genetic risk score composed of the 90 risk loci previously linked to European populations [17].

More recent work from the Global Parkinson’s Genetics Program confirms this differential risk, identifying a novel genetic risk factor in *GBA1* in patients with PD of African ancestry [18]. This supports the need for additional work in this area.

### Objective

The overall objectives of this study are to perform comprehensive phenotyping, compare Black and White persons with PD, and investigate causes of racial disparities, including differences in clinical management and responsible genetic risk factors. The study is partnering with the ongoing Global PD Genetics Program (GP2) [19], which contributes samples and granular phenotypic data from the enrolled participants to enhance our understanding of the genetic architecture of PD in the Black population. The long-term goal of this application is to address the critical gap in knowledge of PD in this underserved population to improve diagnosis, optimize treatment, and plan for clinical trials. The central hypothesis is: PD is phenotypically and genetically different in Black versus White populations, and Black patients receive different and suboptimal clinical management. The research questions this study hopes to answer are as follows: (1) whether Black participants with PD have worse quantitative motor function and cognition, higher levels of depression and disability, and reduced quality of life compared with White participants with PD; (2) whether pharmacological, surgical, rehabilitation, mental health, and telehealth interventions differ by race with underuse of newer or more costly interventions in Black participants with PD; and (3) whether the contribution of genetic factors to PD risk and heterogeneity differs by race.

## Methods

### Overview

The overall strategy is to describe clinical phenotypes, genetic risk profiles, and treatment disparities in the American Black PD population and use the results to develop guidance for educating Black patients and their treating clinicians on how to prevent racial disparities in PD and foster future research opportunities in racial disparities and improve management (Figure 1). This is a multicenter, cross-sectional, case-case, nonrandomized, observational study.

**Figure 1 figure1:**
[figure not shown]
Conceptual model. GP2: Global Parkinson’s Genetic Program; PD: Parkinson disease.

### Study Setting and Design

The 7 study sites are Rush University, University of Maryland, University of Cincinnati, University of Pennsylvania, University of Chicago, Emory University, and Morehouse University (Figure 2). The sites were chosen based on US census data showing higher populations of Black persons in these geographic regions. A total of 400 Black patients with PD and 200 White patients with PD will be recruited. Patients who consent to enroll will have a single study visit encompassing data and sample collection for all 3 aims. A virtual option can also be used to complete questionnaires, followed by an in-person visit for the remaining measures.

**Figure 2 figure2:**

Overview of the organizational structure. GP2: Global Parkinson’s Genetic Program; PD: Parkinson disease.

### Eligibility Criteria

The eligibility criteria are intentionally broad to facilitate the inclusion of diverse samples and ensure the achievement of enrollment targets. Inclusion criteria include age >18 years and fulfilling the Movement Disorder Society Clinical Diagnostic Criteria for Parkinson’s Disease [20]. Patients must self-identify as being Black or White race. Patients must also be able to sign an evaluation to sign consent [21] or have a legally authorized representative (LAR) sign on their behalf. Exclusion criteria include insufficient English to complete study activities or inability to meet idiopathic PD criteria. Eligibility criteria are broad to include representative samples and ensure meeting enrollment targets.

### Recruitment and Screening Strategies

Recruitment will occur in the outpatient movement disorder clinics at the 7 study sites. Treatment clinicians or study coordinators will approach potential participants to discuss participation. Potential participants will be identified by prescreening medical records or by referral to the treating provider. Each White participant was initially matched to be within 5 years of age of the mean age of every 2 Black participants enrolled at the same site. Each time 2 Black participants were enrolled at a site, the study statistician would contact the site with the age range of the next White participant. Part-way through the study, propensity matching replaced this manual process. Potential participants will be interviewed to determine if they meet the eligibility criteria for enrollment.

Black patients with PD have been underrepresented in clinical research [22]. Therefore, study planning includes targeted strategies to facilitate recruitment and foster participant satisfaction with research participation. An advisory board of 6 individuals comprised of Black individuals with PD and family members of affected individuals assists in developing outreach strategies and providing feedback on their study visit experience, with protocol modifications as needed. The patient advisory board members will have participated in the study at 1 of the study sites. Educational strategies include initiatives for both study participants and study staff. A brief video and flip charts with culturally appropriate information are used to improve understanding of participation in research, including the informed consent process [23]. Participation of Black study coordinators is encouraged to foster rapport and cultural sensitivity. Teaching cross-cultural sensitivity is part of the prestudy and annual activities for all site investigators and coordinators [24]. Barriers to recruitment and enrollment will be explored, with each enrolled participant completing a Participations in Clinical Trials Questionnaire that includes a question on barriers to research participation [25]. During quarterly Steering Committee meetings with all site investigators, recent publications on minority recruitment and research are reviewed with the study author.

### Study Assessments and Outcome Measures

Study participants will have a single visit with the site investigator and coordinator after obtaining consent or a hybrid combination of in-person and virtual visits. Recommendations of the NINDS PD CDE Working Group informed the choice of measures, scales, and questionnaires. Data will be collected and entered into a REDCap (Research Electronic Data Capture) system that uses electronic data entry forms. General assessments include demographic data (age, sex, education, and income), medical history, and a confirmatory neurological examination. The remaining assessments fall into 3 categories, namely motor and nonmotor symptoms (Table 1), quality of life and social determinants of health (Table 2), and management of PD (Table 3, Multimedia Appendix 1).

**Table 1 table1:** Motor and nonmotor measures for phenotyping.

Data type or domain and measure or instrument		Description
**Parkinson disease severity**		
	MDS-UPDRS^a^ parts I to IV^b^	Revised, improved version of the MDS-UPDRS for use in PD^c^ studies [26]
	Hoehn and Yahr stages	Common system for staging PD [27]
**Physical function**		
	2-minute walk, 4-meter gait speed, 9-hole pegboard, grip strength, and balance test^b^	To quantitate physical performance relative to available age and gender norms [28]
	Functional reach	A single-item assessment of balance [29]
	Schwab and England Activities of Daily Living Scale	A single-item rating of independent function [30]
	PROMIS Profile-29 Physical Function version 2.0 4a^b^	Measure of disability [31,32]
**Cognitive function**		
	Montreal Cognitive Assessment version 8.3^b^	Detects mild cognitive impairment in PD [33,34]
	Benton Judgment of Line Orientation 15-items	Measure of spatial perception and orientation [35,36]
	Hopkins Verbal Learning Test	Test of verbal short-term memory requiring rapid encoding of information [37]
	Digit span	Measure of verbal working memory [38]
	Semantic fluency	Measures semantic fluency using animal categories [39]
	Symbol Digit Modalities Test^b^	Screens for cognitive impairment [40]
**Mental health**		
	PROMIS Profile-29 depression, anxiety	Measures depression and anxiety
**Pain**		
	PROMIS Profile-29 Pain Interference version 1.1	Measures pain interference with daily life [41]
	PROMIS Profile-29 Pain Intensity version 1.0	Measures severity of pain
**Sleep**		
	Epworth Sleepiness Scale	Measures daytime sleepiness in adults [42]
	PROMIS Profile-29 version 1.0 Sleep Disturbance 4a, PROMIS Profile-29 version 1.0 Fatigue 4a	Measures sleep disturbance and fatigue [43,44]
**Autonomic**		
	Scales for Outcomes-PD Autonomic^b^	Measures autonomic function [45]

^a^MDS-UPDRS: Movement Disorder Society Unified Parkinson’s Disease Rating Scale.

^b^Minimum dataset.

^c^PD: Parkinson disease.

**Table 2 table2:** Quality of life and patient health expectations measures.

Data type or domain and measure or instrument			Description
**Health-related quality of life**			
	The Parkinson’s Disease Questionnaire-8^a^	PD^b^-specific quality of life scale [46]	
**Patient health expectations**			
	Expectations Regarding Movement Scale	Expectations regarding movement with aging [6]	
**Participation in medical research**			
	Trust in Medical Researchers Scale	Likelihood of participation in medical research [47]	
**Social determinants**			
	PROMIS Informational Support version 2.0 4a	Measures access to information and resources [48]	
	Health Stressors Rush Survey	Covers food security, utilities, insurance, transportation, and housing instability	
	PROMIS Profile-29 Ability to Participate in Social Roles and Activities version 2.0 4a	Measures satisfaction with social roles and activities [48]	

^a^Minimum dataset.

^b^PD: Parkinson disease.

**Table 3 table3:** Study assessments for management of Parkinson disease.

Data type or domain and measure or instrument		Description
**Pharmacological management**		
	Parkinson’s Disease Medications Questionnaire^a^	Antiparkinsonian drugs^a^
	Prescribed Non-Parkinson’s Medications Questionnaire^a^	Non-Parkinson drugs
	Unprescribed Drugs Questionnaire	Vitamins, dietary supplements, alternative therapies, recreational drugs, drugs of abuse
**Surgical management**		
	Surgical Questionnaire^a^	DBS^b^, FUS^c^
**Rehabilitation therapy**		
	Rehabilitation Referral Questionnaire^a^	Physical, occupational, speech therapy
	Godin Leisure-Time Exercise Questionnaire, Activity Questionnaire	Exercise and activity [49]
**Mental health and social services**		
	Mental Health and Social Services Referral Questionnaires^a^	Psychiatrist, psychologist, social worker
**Telehealth use and acceptance**		
	Telehealth Use and Acceptance Questionnaire^a^	Perceived usefulness and ease of use [50]
**Participation in clinical trials**		
	Participation in Clinical Trials Questionnaire	Clinical trial participation and barriers to participation
**History of treating clinicians for PD**		
	History of treating clinicians for Parkinson’s disease^a^	Number and types of clinicians, medical visit frequency
**Medical comorbidities**		
	Cumulative Illness Rating Scale-Geriatrics (CIRS-G)^a^	Medical comorbidities [51]
**Self-efficacy**		
	PROMIS Self-Efficacy for Management of Chronic Conditions	Self-efficacy for managing daily activities, symptoms, medications, and emotions [52]
**Health literacy**		
	Rapid Estimate of Adult Literacy in Medicine	Health literacy [53]
	eHealth Literacy Scale	eHealth literacy [54]

^a^Minimum dataset.

^b^DBS: deep brain stimulation.

^c^FUS: focused ultrasound.

Participants who used a LAR for consent can complete assessments with assistance from a research assistant or proxy (care partner). All scales and questionnaires include a check box to document proxy assistance. The scales are administered by the neurologist (site investigator), study coordinator, or other staff as appropriate. The investigator completes the following assessments: MDS-UPDRS [26], Hoehn and Yahr Staging [27], Schwab and England Activities of Daily Living Scale [55], and the Cumulative Illness Rating Scale [51]. The investigator will also complete a questionnaire for the GP2 study that includes demographic and disease-specific information, such as disease duration. The study coordinator administers the rest of the study assessments.

Participants have blood samples drawn and sent to the National Institutes of Health for genetic studies. All participants are also offered enrollment into the Parkinson’s Foundation PD GENEration study in which seven PD genes are examined and results are disclosed to the participant. If the participant consents, an additional blood sample is shipped to the PD GENEration sequencing vendor (Fulgent Genetics). For these participants, genetic counseling, including results disclosure, is performed by either a PD GENEration genetic counselor from Indiana University or the genetic counselor at the Rush University site (either live or through telemedicine).

To optimize recruitment, all Black patients with PD are eligible for enrollment regardless of physical or cognitive impairment level. Therefore, not all patients can complete all study assessments. A minimum dataset, including the primary outcome measures, must be completed, as well as the sample collected for all study participants. The recommended order of study assessments prioritizes outcome measures such that primary outcome measures are completed first, cognitive measures are completed early, and the minimum dataset for all study aims is collected. When a participant cannot complete all study assessments, the site investigator must be contacted. The investigator and coordinator should arrive at a consensus about what assessments will be omitted, and coordinators should record the omitted assessments. The patient can only complete selected study assessments (no proxy assistance permitted), including the cognitive assessments and the “Rapid Estimate of Adult Literacy in Medicine” [25].

### Outcome Measures

The primary outcome measures to characterize PD phenotypes include the NIH Toolbox Motor assessments (2-minute walk, 4-meter walk, balance test, pegboard test, and grip strength) [28]; the Montreal Cognitive Assessment (MoCA), Symbol Digit Modalities Test (SDMT), PROMIS Profile-29 Physical Function, Parkinson’s Disease Questionnaire-8 (PDQ-8), and the MDS-UPDRS. The primary outcome measures to assess PD clinical management include the proportion of participants with antiparkinsonian medications prescribed at the initial visit to the neurologist, the proportion of participants with initial treatment of depression, and the proportion of participants with PD surgical interventions. To characterize genetic risk variants in our sample, the frequencies of the 90 established common PD genetic risk variants based on published genome-wide association studies in a predominantly White population will initially be examined. The study team will also aggregate and summarize sequencing results from PD GENEration, including potential rare variants among 7 established PD genes. The proportion of LRRK2- and GBA-PD will be summarized based on either PD GENEration, which permits comprehensive detection of potential pathogenic alleles, or GP2 genotyping, which can detect many of the most common, recurrent pathogenic variants. Finally, exploratory genotype–phenotype analyses will determine whether established PD risk variants modify clinical manifestations in Black individuals.

### Sample Size

The sample size was calculated for each primary outcome measure described above with 80% power and a 2-sided test to detect a similar effect size observed from our pilot data (Table 4). Bonferroni correction was applied to control the overall significance level at .05. The minimal sample size for these analyses requires 365 Black and 183 White participants to complete this aim. The data observed in 3 studies guided the sample size calculation for PD clinical management (White vs non-White or Black: 78% vs 62% for measure 1 [4], 92% vs 80% for measure 2 [56], and 10% vs 0.4% for measure 3 [57]). The sample size was calculated using 90% power and a 2-sided test for each primary measure. Bonferroni correction was applied to control the overall significance level at .05. With a 1:2 ratio, the largest sample size required among all 3 measures is 173 White patients with PD and 346 Black patients with PD. For the genetic studies, our sample size will permit exploratory analyses, and all data will be contributed to GP2 for fully-powered meta-analysis.

**Table 4 table4:** Pilot data effect sizes for sample size calculation.

Primary measures	White patients with PD^a^ (n=25), mean (SD)	Black patients with PD (n=25), mean (SD)
4-meter walk computed score	1.1 (0.2)	0.8 (0.3)
Balance *t* test score	47 (12)	32.7 (13.1)
Pegboard dominant score	33.2 (10.9)	41.4 (15.6)
MoCA^b^	27 (2)	23.3 (3.1)
SDMT^c^	49.6 (9.1)	39.4 (14.1)
PDQ-39^d^	12.8 (7.9)	22.5 (12.3)

^a^PD: Parkinson disease.

^b^MoCA: Montreal Cognitive Assessment.

^c^SDMT: Symbol Digit Modalities Test.

^d^PDQ-39: Parkinson’s Disease Questionnaire.

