### Statistical Analysis

Each primary outcome measure will be compared between Black and White patients with PD. Bonferroni correction will be applied. The primary outcome measures are a 4-meter walk computed score, Balance test *t* score, Pegboard dominant *t* score, MDS-UPDRS motor score [26], MoCA [33], SDMT [58], PROMIS Profile-29 Physical Function, and PDQ-8 [46]. For significant measures, linear regression analysis will be performed to examine further the difference between the 2 groups with adjustment for age, sex, and disease duration. The interaction effects of race with these 3 variables will be explored. Regression analysis for cognitive measures will adjust for depression and anxiety scales in addition to these demographics. Regression will also be adjusted for comorbidities using the Cumulative Illness Rating Scale-Geriatrics score. The study site effect will be controlled as a random effect in the model. All analyses will be done using SAS (version 9.4).

For the PD management analysis, each primary outcome measure will be compared between Black PD and White PD groups using the chi-square test or Fisher exact test. Bonferroni correction will be applied. A hierarchical logistic regression analysis will assess the determinants of racial disparities in management. Besides race, age, sex, and education, income, symptom severity, and comorbidities will be included in the model. The interaction effect of race with those variables will be explored. The study site effect will be controlled as a random effect in the model. Secondary analyses will investigate differences between White PD and Black PD groups in other clinical management measures, including telehealth, participation in clinical trials, and rehabilitation therapy.

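### The Aim 1 minimum of 365 Black and 183 White participants does not follow from the pilot effects in Table 4, and several primary measures have no pilot effect, so the 80% power statement is unsupported as written

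*Protocol article*

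**What the plan says.** The Sample Size section describes the Aim 1 calculation in these terms:

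- Scope and power: "The sample size was calculated for each primary outcome measure described above with 80% power and a 2-sided test".
- Source of the effects: "to detect a similar effect size observed from our pilot data (Table 4").
- Multiplicity: "Bonferroni correction was applied to control the overall significance level at .05". The divisor is not given.
- Result: "The minimal sample size for these analyses requires 365 Black and 183 White participants to complete this aim".

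Table 4 has six rows: 4-meter walk, balance, pegboard, MoCA, SDMT and PDQ-39, each with 25 pilot participants per group.

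The lists of primary measures are longer. Statistical Analysis names eight: 4-meter walk, balance and pegboard, followed by "MDS-UPDRS motor score [26], MoCA [33], SDMT [58], PROMIS Profile-29 Physical Function, and PDQ-8 [46"]. Outcome Measures also names the 2-minute walk and grip strength, which makes ten if the MDS-UPDRS counts once. Background says that the pilot groups did not differ significantly in "Hoehn and Yahr stage, or Movement Disorder Society-Unified PD Rating Scale (MDS-UPDRS) part III Motor scores", and gives no means or SDs for that scale.

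**The concern.** The section gives a power, a source of effect sizes and a result, so a reader can repeat the calculation. The pilot effects are large, and large effects do not lead to 548 participants. The table offered as the source also covers only part of the list of primary measures, although the text says that the calculation was done for each of them.

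At stake is how the results will be read. Someone told that every primary measure has 80% power at its pilot effect could take a null MDS-UPDRS motor or PROMIS Physical Function result as evidence against a difference of pilot size. For those measures the document gives no pilot effect.

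**Working it through.** **Inputs.** Means and SDs come from Table 4. Power is 80%, two-sided. The White:Black ratio is 1:2, which is stated for Aim 2 and which 183:365 follows. The Bonferroni divisor m is an assumption. I used 6 (rows in Table 4), 8 (list in Statistical Analysis) and 10 (list in Outcome Measures).

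**Step 1. Check the method on Aim 2.** The same section states: "With a 1:2 ratio, the largest sample size required among all 3 measures is 173 White patients with PD", with 346 Black. For 92% vs 80%, alpha .05/3, 90% power, 1:2, and the usual two-proportion formula with pooled variance under the null, I get 172.7, so 173 White and 346 Black. The 78% vs 62% measure gives 167 and the 10% vs 0.4% measure gives 95. The Aim 2 figure reproduces exactly.

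**Step 2. Standardised effects.** d = |mean difference| / sqrt((SD_W² + SD_B²)/2). For pegboard, 8.2 / sqrt((10.9² + 15.6²)/2) = 8.2 / 13.46 = 0.61.

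**Step 3. Required White n** (two-sample t-test; Black is about twice this):

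| Row | d | m = 6 | m = 8 | m = 10 |
|---|---|---|---|---|
| 4-meter walk | 1.18 | 15 | 16 | 16 |
| Balance | 1.14 | 16 | 17 | 17 |
| Pegboard | 0.61 | 51 | 53 | 56 |
| MoCA | 1.42 | 11 | 11 | 12 |
| SDMT | 0.86 | 26 | 28 | 29 |
| PDQ-39 | 0.94 | 22 | 24 | 25 |

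Normal-approximation check for pegboard at m = 8: n_W = 1.5 × (2.734 + 0.842)² / 0.609² ≈ 52, against 53 from the t-test. The largest requirement is therefore 53 White and 106 Black at m = 8. The stated 183 is 183/53, or about 3.5 times that (183/51 ≈ 3.6 at m = 6; 183/56 ≈ 3.3 at m = 10).

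**Step 4. Could another convention give 183?** White n for pegboard at m = 8:

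- 90% power: 67
- larger of the two SDs: 71
- 20% dropout: 67
- allocation ratio reversed: 104
- larger SD, rank-test efficiency 0.864 and 20% dropout together: 103, or 153 at 95% power

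None reaches 183. Four times the unequal-variance pegboard n at .05/8 is 182.9, but nothing in the document supports a factor of four, so I treat that as coincidence.

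**Step 5. What 183/365 does correspond to.** d = (z_alpha + z_beta) × sqrt(1/183 + 1/365) = (2.734 + 0.842) × 0.0906 = 0.324 at m = 8. By the t-test:

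| Sample (White/Black) | m = 6 | m = 8 | m = 10 |
|---|---|---|---|
| 183/365 | 0.316 | 0.325 | 0.332 |
| 200/400 | 0.302 | 0.311 | 0.317 |

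No row of Table 4 has an effect this small.

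**Step 6. Power at 183/365.** For pegboard at m = 8, 0.609/0.0906 − 2.734 ≈ 4.0, so power is above 99.9%. With the larger SD, d = 8.2/15.6 = 0.526, and power is still above 99.8% for m from 6 to 10. The other five rows have more. For a measure with no pilot value, power at m = 8 would be about 30% at an assumed d of 0.20, 51% at 0.25, 71% at 0.30 and 95% at 0.40.

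**Step 7. Coverage.** Against Statistical Analysis, MDS-UPDRS motor and PROMIS Physical Function have no row. Against Outcome Measures, the list that precedes the sample size text, 2-minute walk and grip strength have none either. PDQ-8 appears only through PDQ-39.

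**The case against.** The strongest reply is that 365/183 is the minimum covering all primary measures, and that the limiting one may not be in the table. Pilot MDS-UPDRS part III data evidently exist. With 25 per group, a non-significant result at .05 fits any observed difference up to about 2.011 × sqrt(2/25) ≈ 0.57 SD (assuming an unadjusted t-test), so an effect near 0.32 is possible. The article also condenses a fuller protocol. This stands to the extent that the calculation itself may be sound. It does not remove the inconsistency, because the article names Table 4 as the source of the effects and the result does not follow from it.

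A second reply is that a sample larger than needed does no harm. For the six tabulated effects that is right.

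A reader might go further and infer that the study is underpowered, that its size is wrong, or that a null MDS-UPDRS motor or PROMIS result could not be interpreted. The documents support none of these. No effect is given for the untabulated measures, so their power cannot be called low. A null result can still be read with its confidence interval and against a detectable difference of about 0.33 SD.

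Using PDQ-39 to plan for PDQ-8 is a reasonable proxy and the row is labelled as such. The pegboard row is a score in Table 4 and a t score in Statistical Analysis. Both are minor labelling points.

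**Conclusion.** The point holds as an unsupported figure and power statement. The Table 4 effects require about 53 White and 106 Black participants at .05/8, not 183 and 365. The stated size corresponds to about 0.32 to 0.33 SD, from a source that the article does not disclose. The 80% figure greatly understates power for the six tabulated effects, with PDQ-8 covered only by proxy. It has no stated basis for MDS-UPDRS motor and PROMIS Physical Function, nor for 2-minute walk and grip strength if the Outcome Measures list governs.

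This rests on an averaged variance, a two-sample t-test, a 1:2 ratio and an assumed divisor of 6 to 10. The gap is too wide for any of these choices to close. The enrolment target is not in question.

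**What to change.** 1. Reconcile the primary measures in Outcome Measures and Statistical Analysis, and state the Bonferroni divisor that follows.
2. Replace the Aim 1 power sentence with the detectable difference. If there are eight measures: 80% power at two-sided .05/8 for about 0.33 SD with 183 White and 365 Black, and about 0.31 SD with 200 and 400. For divisors 6 to 10 the ranges are 0.316 to 0.332 and 0.302 to 0.317.
3. State which measure and effect produced 365/183 and add its row to Table 4, or say that no pilot effect supports the untabulated measures.

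The cost is a few sentences and possibly a table row. Enrolment does not change.
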